## Abstract

**Background:**

Work-related neck pain (WRNP) is a leading cause of disability and absenteeism. Patients with neck pain often have neck muscle tenderness and decreased cervical mobility, which are sometimes combined with psychosocial issues, such as pain catastrophising, thereby reducing their work ability. Whilst multidisciplinary treatments, including pharmacological interventions, manual therapy and specific neck exercises, have produced positive outcomes, effective personalised treatment modalities are still needed. Furthermore, manual therapies using the hands can bring fatigue to therapist. Occiflex is a computerised device that can provide personalised segmental joint mobilisation based on symptoms and injury of the patient and then provide a medium range of joint activities to improve range of cervical motion. This study aims to compare the effect of computerised mobilisation performed with Occiflex with that of traditional manual therapy on WRNP.

**Methods:**

We will conduct a prospective randomised controlled trial including 150 patients with WRNP. These patients will be randomly assigned to one of three groups: (i) home exercise (TE), (ii) home exercise plus Occiflex therapy and (iii) home exercise plus manual therapy delivered by a physical therapist. Ten treatment sessions will be performed in four weeks. During the trial, these patients will receive only the assigned treatment and the standard patient education and will be asked not to use any analgesics unless strictly necessary. Assessments by trained evaluators will occur at baseline, week 4 and week 12. The primary outcome measures will include visual analogue scale (VAS) for pain and neck disability index (NDI) at each time point. Secondary outcome measures will include cervical range of motion (CROM), pressure pain threshold (PPT), global perceived effect (GPE) and sick leave. Group by time differences will be analysed using linear mixed models with repeated measures.

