### Objective

The objective of this article is to introduce a protocol for comparing the effects of computerised mobilisation performed with Occiflex with those of traditional manual therapy on WRNP. By adding these two mobilisation techniques to a standard exercise programme, this article also determines whether computerised mobilisation or manual therapy produces more benefits than pure exercise intervention. Computerised mobilisation is assumed to be superior to manual therapy and generate more effects than exercise alone.

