### Sample size calculation

The sample size will be calculated using PASS 15.0.5 based on the means, standard deviations and an alpha of 5% (0.05) with a unilateral contrast. Assuming that the standard deviation of NDI scores is 8, then 38 participants per group will give the study 80% power to detect minimum clinically important differences (MCID) of 5 units in NDI [34]. Meanwhile, 41 participants per group are required based on the 10 cm VAS scale with a standard deviation of 5 and a clinically significant difference of 3 points [26]. To accommodate an expected dropout rate of 20% during follow-up and to have sufficient statistical power for the different variables in this study, a total of 150 participants will be sufficient.

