### Statistical analysis

The statistical analysis will be carried out using the IBM SPSS Statistics 26 software. Descriptive statistics will be used to describe the study population and will be summarised per group based on the number of observations, means and standard deviations. The primary and secondary outcome variables (VAS, NDI, CROM, PPT and GPE) will be analysed by intention to treat and by using linear mixed models with repeated measures. The linear mixed model requires the residuals to be normally distributed. The Shapiro–Wilk test will be applied to test the normality. In case of a non-normal distribution of the residuals, an appropriate non-parametric test will be conducted. Multiple post-hoc comparisons will be conducted through Bonferroni’s contrast for parametric distributions. All tests will be two sided, and the level of significance is set to 0.05. The missing data in this study will be handled with a mean imputation or mixed modelling approach.

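### The Occiflex versus manual therapy comparison is tested only as one of several post-hoc Bonferroni pairs, with no priority, at an avoidable cost in power

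*Protocol article*

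**What the plan says.** The abstract's Background and Discussion, and the article's Background section, present the trial as a comparison of Occiflex with traditional manual therapy, and the Background section justifies it by the lack of any randomised comparison of the two. The Objective section adds the question whether either mobilisation technique improves on exercise alone, and gives a directional hypothesis: "Computerised mobilisation is assumed to be superior to manual therapy and generate more effects than exercise alone".

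The analysis is described in two places. The abstract's Methods says "Group by time differences will be analysed using linear mixed models with repeated measures". The Statistical analysis section specifies linear mixed models with repeated measures and then: "Multiple post-hoc comparisons will be conducted through Bonferroni’s contrast for parametric distributions". It also says "All tests will be two sided, and the level of significance is set to 0.05". Neither place says which pair of arms, or which set of pairs, carries the main conclusion.

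The Sample size calculation names no pair of arms either. It uses "an alpha of 5% (0.05) with a unilateral contrast" with no adjustment for several pairs: "Assuming that the standard deviation of NDI scores is 8", "then 38 participants per group will give the study 80% power" for a 5-point difference in NDI.

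**The concern.** A comparison that is the reason for the trial, and that carries a hypothesis stated in advance, is a planned contrast. The Statistical analysis section treats it as post-hoc and gives it the same share of alpha as the two contrasts against exercise. Two things are at stake.

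- **Power.** The head-to-head is tested at a stricter level than the sample size assumed, and stricter than error control over three arms requires.
- **Interpretation.** With no contrast named in advance, the choice of which comparison to lead with is open when the results are written up.

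This point concerns the arm contrasts for one outcome at one visit. Having two primary outcomes and two follow-up visits is a separate matter and is not counted here.

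**Working it through.** **Inputs from the protocol.** NDI: SD 8, difference 5. VAS: SD 5, difference 3. Three equal arms, 150 in total, 20% dropout, so 150/3 × 0.8 = 40 evaluable per arm. Tests are two-sided at 0.05. That there are three pairs is inferred from three arms; the protocol does not give the number.

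**The plan's own figure.** For two groups at one-sided 0.05 and 80% power, n = 2 × [8 × (1.645 + 0.842)/5]² = 31.7, so 32 per arm. Two-sided it is 41. The stated 38 matches neither. It does match a three-arm F test with one arm 5 points from the other two (power 0.800 at n = 38), and also 31.65 × 1.2 = 37.99. The article does not say which route was used, so nothing below rests on the 38.

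**Power for Occiflex versus manual therapy, one unadjusted visit.**

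The standard error is SD × √(2/40), and the noncentrality is the difference divided by the standard error. The variance is pooled over three arms, giving 117 df. Critical t is 1.980 at 0.05 and 2.429 at 0.0167.

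- NDI: 5/(8 × 0.2236) = 2.795. Power is 79.2% at 0.05 and 64.3% at 0.0167.
- VAS: 3/(5 × 0.2236) = 2.683. Power is 75.8% at 0.05 and 60.1% at 0.0167.

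Normal check for NDI: Φ(2.795 − 1.960) = 79.8% and Φ(2.795 − 2.394) = 65.6%.

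**Cost in participants.** The ratio of sample sizes for 80% power is (2.394 + 0.842)²/(1.960 + 0.842)² = 10.47/7.85 = 1.33. For NDI that is 54 instead of 41 evaluable per arm. The ratio does not depend on the variance, and so not on the correlation.

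**Sensitivity to the within-person correlation ρ.** The protocol gives none, so 0.3 to 0.7 is an assumption, as are equal correlation between visits and an equal effect at both follow-up visits. The variance of the outcome analysed is 64 × 2(1 − ρ) for change at one visit, 64 × [(1 + ρ)/2 + 1 − 2ρ] for mean change over both visits, and 64 × (1 − ρ²) for one visit adjusted for baseline. NDI power at 0.0167 / at 0.05:

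| ρ | Change, one visit | Mean change, two visits | One visit, baseline-adjusted |
|---|---|---|---|
| 0.3 | 48% / 65% | 62% / 77% | 69% / 83% |
| 0.5 | 64% / 79% | 79% / 89% | 79% / 89% |
| 0.7 | 88% / 95% | 96% / 98% | 93% / 97% |

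**Shaffer step-down for three groups.** The smallest p is tested against 0.05/3 and, if that is rejected, the other two each against 0.05. This is valid because, once one pairwise equality is false, at most one of the other two can be true. In 200,000 simulated trials (NDI, one unadjusted visit, 40 per arm), head-to-head power was:

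- 72% when manual therapy equals exercise;
- 79% when Occiflex is 10 points and manual therapy 5 points better than exercise;
- 66% when exercise lies midway between the two, an ordering the hypothesis does not foresee.

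The false-positive rate for a pair that truly did not differ stayed below 0.05 (about 0.049 at most).

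**The case against.** **Bonferroni is valid and matches the Objective section.** That section covers all three pairs and does not rank them in its hypothesis sentence. This stands in part: treating the three pairs as co-equal is defensible. It does not rescue plain Bonferroni, because the step-down rejects everything Bonferroni rejects at the same familywise error.

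**This is detail for the analysis plan.** A condensed article may leave the model contrasts to a fuller document. But the article does not stay silent; it chooses a pairwise procedure and labels it post-hoc.

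**The 64% is too pessimistic.** The planned model uses repeated measures. This stands for the absolute figure: the table runs from 48% to 96%. The stricter level remains, and so does the factor of 1.33.

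**A stronger reading that a reader might infer.** One could take the group-by-time test as an overall three-arm gate that would declare the trial positive even if Occiflex and manual therapy were the same. If both beat exercise by 5 points and do not differ, a three-arm F test at one visit is indeed significant in about 82% of trials. That is not an error rate: exercise really is worse, so rejecting is correct and answers part of the stated objective. The planned pairwise test would then find Occiflex different from manual therapy in only about 1.7% of trials. The protocol nowhere says that the overall test decides the trial or gates the pairwise tests, so the documents do not support that reading.

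**Conclusion.** The point holds in a limited form. The head-to-head that motivates the trial has no priority in the analysis and, on the natural reading of three pairs, is tested at two-sided 0.0167. For one unadjusted visit with 40 per arm, this lowers NDI power from about 79% to about 64% (VAS from about 76% to about 60%), or equivalently needs about a third more participants for 80% power. Over the correlations assumed above, the loss ranges from about 17 percentage points to about 3; it is smallest where power is already high.

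The finding is not that the error rate is uncontrolled, nor that a significant result would be false. A better procedure is available at almost no cost. The trial can be analysed as it stands, so this is a change that should be made rather than one that must be.

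**What to change.** In the Statistical analysis section, replace the post-hoc Bonferroni rule with planned contrasts from the mixed model, and adopt one of two procedures. They should not be combined, because the step-down gives no contrast priority.

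1. **Preferred.** Name Occiflex minus manual as the primary contrast, tested at two-sided 0.05. Occiflex minus exercise and manual minus exercise are supporting contrasts. They are either labelled secondary or tested for confirmation only if the primary contrast is significant. In the latter case each can be tested at 0.05, since at most one of those two equalities can then still be true. Cost: if Occiflex and manual therapy do not differ, there will usually be no confirmatory claim against exercise.
2. **If the three pairs are to stay co-equal.** Use the three-group Shaffer step-down as set out above. It can be applied by hand to the unadjusted p-values from SPSS. Cost: simultaneous confidence intervals are less direct than with Bonferroni.

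Under either option, add that any claim about Occiflex versus manual therapy rests on that contrast and its confidence interval, not on the overall group-by-time test. The model, data and software are unchanged. The choice should be fixed and dated before any outcome data are compared by arm.

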**Discussion:**

This protocol describes the methods for a randomised controlled trial to compare the effectiveness of computerised versus manual mobilisation techniques in treating WRNP. The results will provide an alternative method (Occiflex) that is possibly effective for treating neck pain whilst minimising the manual work done by therapists.

**Trial registration:**

The study protocol was retrospectively registered at http://www.chictr.org.cn (registration number: ChiCTR2100053076) on November 10, 2021.

## Background

Work-related neck pain (WRNP) is a leading cause of disability and absenteeism in our society [1]. Such condition is highly prevalent amongst office workers, which may be partly due to their working environment, prolonged working hours and psychosocial factors [2, 3]. Sedentary work for extended periods of time may result in excessive neck muscle activity and fatigue [4], whilst poor postural habits [3] and maladaptive motor control [5] contribute to the development of pain and fatigue of the neck muscles. The origin of WRNP is likely multifactorial, especially in the case of chronic pain. Patients with WRNP show a range of symptoms, including neck stiffness, upper extremity pain, headache and, in some cases, psychological problems, such as depression, anxiety and pain catastrophising [6]. These problems not only pose a burden for individual workers but also lead to substantial costs for the whole society [1].

Amongst the conservative treatments for neck disorders, physical therapy is widely used in clinical practice. Exercise and manual therapy are recommended for treating many types of neck pain [7] and remain a priority for researchers. Several studies have proven that exercise can improve pain and disability in chronic non-specific neck pain [8, 9]. For instance, Andersen et al. found that one year-physical exercise intervention can improve the overall pain perception of office workers with chronic musculoskeletal pain, indicating a significant decrease in central sensitisation [10]. Mobilisation of the spine and other manual therapies have also shown promising effects yet inconclusive results according to several meta-analyses [11–13]. Though these techniques have been reported to elicit hypoalgesia and reverse pain sensitisation [14], the manual force applied by physical therapists during cervical mobilisation is largely inconsistent [15, 16]. In practice, having the same therapist repeat the techniques with precision and consistency over time can be challenging partly because of the manual technique or the therapist’s fatigue. Moreover, practitioners show some differences in the manual techniques they apply in each therapeutic session (i.e., manipulation and mobilisation). In addition, spinal manipulation has been reported to cause mild to moderate adverse effects when performed on the upper spine possibly due to the inconsistencies in the technique and manually applied force. Manual therapy is widely used by physical therapists yet should be applied with caution especially during the administration of high-velocity or aggressive techniques [17].

To overcome the inherent disadvantages and safety issues related to manual therapy, researchers have developed a device capable of 3D computerised neck mobilisation. This device, called Occiflex™, enables therapists to implement a hands-free, sustained mid-range neck mobilisation for patients. This device comprises an adjustable bed and a cradle that is capable of any movement in a 3D space with six degrees of freedom [18]. Before the treatment process, the therapist should teach the device a series of individualised mobilisations for each patient based on their impairment. Subsequently, the Occiflex can carry out the recorded mobilisation automatically and precisely in a slow and smooth manner whilst avoiding the end of the available neck range of motion. Pilot studies have examined the safety of computerised mobilisation and revealed that the continuous and accurate mid-range mobilisation of the cervical spine can reduce neck muscle contraction, alleviate pain and increase cervical range of motion (CROM) [18–20]. River et al. explained that patient-reported improvements may be associated with reduced afferent pain and diminished central sensitisation following the computerised mobilisation. However, no randomised study has compared the effects of computerised mobilisation with those of manual therapy on WRNP.

### Objective

The objective of this article is to introduce a protocol for comparing the effects of computerised mobilisation performed with Occiflex with those of traditional manual therapy on WRNP. By adding these two mobilisation techniques to a standard exercise programme, this article also determines whether computerised mobilisation or manual therapy produces more benefits than pure exercise intervention. Computerised mobilisation is assumed to be superior to manual therapy and generate more effects than exercise alone.

## Methods/design

A prospective, three-armed, open-label randomised controlled trial of patients with WRNP will be conducted in the out-patient physiotherapy department of the Sixth Affiliated Hospital, Sun Yat-sen University.

### Ethics approval

The study design and procedures were approved by ethics committee of the Sixth Affiliated Hospital, Sun Yat-sen University (Protocol Number: 2021ZSLYEC-317) and qualified for registration in the Chinese Clinical Trial Registry (ChiCTR2100053076). All participants must provide their informed written consent prior to their enrolment in the study.

### Sample selection

Individuals with WRNP will be screened via an online questionnaire by a physiotherapist and will be selected based on the eligibility criteria [4, 5] listed in Table 1. Before enrolment, each participant should undergo a physical assessment, including medical history, neurological test and special testing, to be administered by another therapist. Those who pass the preliminary screening would be further examined by a physician to exclude definite pathological factors, such as tumours and fractures, via an X-ray imaging test. Figure 1 shows the flowchart of the research protocol.

**Fig. 1 Fig1:**
[figure not shown]
Flowchart of research protocol

**Table 1 Tab1:** Inclusion and exclusion criteria

Inclusion criteria
**• **Age: 18 and 55 years • Office workers performing at least 4 h of computer work per day (on average) • Current neck pain, with or without pain in head or arm region • Experiencing pain for least 3 months, at a moderate or high pain intensity (≥ 5 of 10, Visual Analog Scale) • No cognitive impairment and volunteer to participate in the study
Exclusion criteria
• Pain caused by definite pathological factors, such as cerebrovascular diseases involving vertebral arteries, spinal cord pathology, cervical cancer or fracture • Neck pain secondary to diseases such as rheumatoid arthritis, ankylosing spondylitis and cervical spine infection • Suffering from cervical myelopathy or radiculopathy, coupled with motor, reflex, and/or sensory changes in the upper limb • Recurrent vertigo, or dizziness • Previous surgery to the cervical spine

### Randomisation

After completing the baseline assessment, the eligible subjects will be randomised in equal portions to the home exercise group, Occiflex group and manual therapy group via a computer-generated block allocation with a block size of 6 or 9. Randomisation will be stratified by the baseline score (≤ 25 vs. ≥26 on a 0–50 scale) on the neck disability index (NDI) and balanced by gender in a 2: 1 ratio (female vs. male) for each group. This procedure ensures that the participants with the same severity of neck disability will be allocated to each group and that all groups are comparable in sex. Both the entry process and group allocation are unblinded to the researchers, examiners and participants.

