### Outcome measures

Personal information, including age, gender, BMI, international physical activity questionnaire (IPAQ) [24], working years and time since the onset of symptoms, will be collected at the baseline. The primary outcome measurements will include the VAS for pain and NDI to be administered at weeks 4 and 12. Secondary outcomes will include CROM, pressure pain threshold (PPT), global perceived effect (GPE) and sick leave. These evaluations will be carried out by an evaluator trained with these procedures. The adverse reactions during therapy will also be recorded.

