#### Pressure pain threshold (PPT)

The PPT is recorded using the digital algometer FPX-25 (Wagner Instruments, Greenwich, CT) to measure the midpoint of the bilateral trapezius muscle and the spinous process of the vertebra C2 [30]. The therapist gradually increases the pressure until the participant complains of pain or discomfort. PPT has reported high intra- and inter-rater reliabilities (ICC = 0.94–0.97; ICC = 0.79–0.90, respectively) amongst patients with neck pain[31]. The measurement should be repeated three times, and the average scores should be computed. The PPT will be assessed at the baseline, week 4 and week 12 of the study period.

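### The protocol describes an open entry process, so upcoming assignments are not concealed from study staff; examiners of CROM and PPT also know the arm, a lesser matter.

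*Protocol article*

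**What the plan says.** The Randomisation section of the protocol article fixes the following:

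- **Order of events:** "After completing the baseline assessment, the eligible subjects will be randomised".
- **Ratio:** participants are "randomised in equal portions to the home exercise group, Occiflex group and manual therapy group".
- **Method:** "computer-generated block allocation with a block size of 6 or 9", stratified by baseline NDI in two levels and balanced by gender. The article does not say whether the two sizes are mixed at random or whether staff know them.
- **Openness:** "Both the entry process and group allocation are unblinded to the researchers, examiners and participants".

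Methods/design describes the study as follows: "A prospective, three-armed, open-label randomised controlled trial of patients with WRNP".

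Sample selection puts the entry decision with staff: a physiotherapist screens, another therapist performs the physical assessment, and a physician examines those who pass.

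On measurement, Outcome measures says "These evaluations will be carried out by an evaluator trained with these procedures", and the PPT section says "The therapist gradually increases the pressure until the participant complains of pain or discomfort". CROM and PPT are secondary outcomes. VAS and NDI are primary and self-reported. No section describes a concealed sequence or a masked assessor.

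**The concern.** The openness sentence names two separate things, entry and allocation, and opens both. Participants and treating therapists must know the treatment once it is assigned. Nothing in the design requires staff to know, or be able to predict, the assignment of someone not yet enrolled.

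The entry decision involves judgement. Criteria such as recurrent dizziness, or radiculopathy with sensory change, leave room for discretion. The Objective and Discussion also declare an expected result, namely that the device is superior to manual therapy and better than exercise alone. Staff who know or can guess the next arm could admit, defer or exclude a candidate accordingly. The groups would then differ in ways nobody recorded. The linear mixed model in Statistical analysis cannot adjust for unmeasured selection, so VAS and NDI would be affected along with everything else.

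A second and smaller matter is that examiners who know the arm could, without intending to, influence the CROM and PPT readings.

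**Working it through.** The plan gives no figure for predictability, so there is none to reproduce. The check asks how much of the next assignment can be foreseen under each reading of the openness sentence.

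**Inputs (Randomisation):** three arms at 1:1:1; blocks of 6 (2 per arm) or 9 (3 per arm). With no information, a guess is right 1/3 = 33.3% of the time.

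**Case A: the list itself is visible.** The next assignment is known outright, whatever the block size.

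**Case B: past allocations visible, block size known.** The best guess is the arm with most places left in the block, and it is right with probability (places left for that arm) / (places left in the block). For a block of 6, averaging over all possible paths:

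| Position | Probability that the best guess is right |
|---|---|
| 1 | 2/6 = 0.333 |
| 2 | 2/5 = 0.400 |
| 3 | 2/4 = 0.500 |
| 4 | (2/5)(1/3) + (3/5)(2/3) = 0.533 |
| 5 | (1/5)(1) + (4/5)(1/2) = 0.600 |
| 6 | 1.000 |

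The sum is 3.367, and 3.367/6 = 56.1%. The same enumeration for a block of 9 gives 4.787/9 = 53.2%.

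An assignment is certain when only one arm has places left:

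- Block of 6: the last place always, and the last two when they are the same arm (probability 1/5). 1 + 1/5 = 1.2 per block; 1.2/6 = 20.0%.
- Block of 9: 1 + 2/8 + (2/8)(1/7) = 1.286 per block; 1.286/9 = 14.3%.

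At least one arm can be ruled out for 46.7% of assignments (block of 6) or 35.7% (block of 9).

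**Case C: past allocations visible, sizes 6 and 9 mixed at random and not disclosed.** A 50:50 mix is assumed, because the article gives no proportion. The guesser updates the probability of each block size after every allocation. Simulation with 800 sequences per length gives:

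| Sequence length | Best guess right | Certain | At least one arm ruled out |
|---|---|---|---|
| 150 (one list) | 54.1% | 5.1% | 13.7% |
| 75 (150/2) | 53.7% | 5.2% | 14.1% |
| 38 (150/4, rounded) | 53.2% | 4.7% | 13.4% |

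Varying undisclosed sizes therefore reduces certainty from 14-20% to about 5%, but leaves the best guess well above chance. Concealing the sequence is what matters most; varying the block size is an addition to it. The gender balancing in Randomisation is not modelled in any case.

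**Examiner knowledge: no arithmetic applies.** Baseline precedes randomisation, so knowing the assigned arm can affect only the week 4 and week 12 readings. Two of the measured outcomes involve an operator: PPT pressure is raised by hand, and CROM is taken with a device. Both are secondary.

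**The case against.** - **The sentence may only be a loose way of saying open-label.** It does not say the sequence can be seen in advance, and eligibility and baseline come before randomisation. This stands as a caution: reading the researchers as the recruiting staff, and open entry as unconcealed entry, is an inference. It is nevertheless the natural reading, since entry is named separately from allocation and no other section provides concealment. If concealment exists, the sentence is wrong as written and still needs correcting.
- **The article is condensed.** This does not answer the point, because the article makes a positive statement of openness and is not merely silent.
- **The certainty figures could be overstated.** A reader might infer that one assignment in five is known in advance. That requires a block of 6 whose size staff know. The article's wording on block size may already mean varying sizes, in which case about 5% applies. This stands, and the figure must be given as a range.
- **PPT and the treating therapist.** A reader might infer that the treating therapist measures PPT. The PPT section says only that a therapist applies the pressure; the Abstract and Outcome measures assign assessments to trained evaluators.
- **Examiner bias as fact.** A reader might infer that examiner knowledge does shift CROM and PPT in favour of the device. The documents support only that it could. The PPT endpoint is the participant's own report, averaged over three readings, and CROM is read from a device. Both limit examiner influence without removing it.
- **Masking examiners leaves the primary outcomes exposed.** True: VAS and NDI are reported by participants who know their arm.

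**Conclusion.** The concealment defect holds as written: the protocol describes an entry process open to study staff, and open-label treatment does not require it. If the list is visible, prediction is complete. If only past allocations are visible, a best guess is right about 53-56% of the time against 33%, with about 5% to 20% of assignments certain. The lower end assumes sizes 6 and 9 mixed 50:50 and undisclosed; the upper end assumes blocks of 6 with the size known.

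These figures measure the opportunity for selection. The documents do not show that selection has taken place, nor how large or in which direction the resulting bias would be. The opportunity bears on all outcomes, including the primary ones, and cannot be repaired at analysis, so the sentence should not stand.

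Examiner knowledge of the arm is a lesser point. It could bias two secondary outcomes, CROM and PPT, and would not by itself call for a change of the same urgency.

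**What to change.** Replace the openness sentence in Randomisation with a statement that:

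1. someone not involved in enrolment generates and holds the sequence;
2. each assignment is released, by web list or sequentially numbered opaque sealed envelopes, only after eligibility, consent and baseline are complete;
3. block sizes are varied and withheld from recruiting staff;
4. participants and treating therapists know the treatment after assignment.

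The trial was registered retrospectively, and the article gives no enrolment start date. If enrolment has begun, concealment can apply only to later participants, and the report should say how the earlier ones were allocated.

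As a secondary improvement, state in Outcome measures that the trained evaluators take the week 4 and week 12 CROM and PPT readings without knowledge of the arm, and ask participants not to reveal it. This uses a role already planned.

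The cost is minor logistics: envelopes or a simple web list, and a duty-roster rule for the evaluators. Treatments and sample size do not change.
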